## Assignment of interventions: allocation

### Sequence generation {16a}, concealment mechanism {16b}, implementation{16c}

Patients will undergo randomization after informed consent is given. Randomization will be performed with the randomization module of the web-based database program REDCap (Research Electronic Data Capture, REDCap, Vanderbilt University 2016). The allocation sequence is based on computer-generated random numbers without stratification. The allocation table is generated in a separate file uploaded to the REDCap randomization module before the database is going to the production status.

## Assignment of interventions: blinding

### Who will be blinded {17a}, procedure for unblinding if needed {17b}

The randomizing physicians are blinded to the allocation table. Due to the nature of the study, the assignment to the study intervention (diagnostic test) and the image interpretation will be performed open-label. Furthermore, TAVR operators are not blinded. Study personnel responsible for the evaluation of end-points will be blinded regarding the allocated intervention. Unblinding procedures are not necessary due to the open-label design of the study.

## Data collection and management

### Plans for assessment and collection of outcomes {18a} and plans to promote participant retention and complete follow-up {18b}, methods to handle non-adherence and missing data {20c}

Patient data will be pseudonymized for study purposes. All patient data will be assessed on a paper-based CRF. Variables will be entered from clinical available source data (patient record) or via direct entry based on the information given by patients or the clinical examination. For the purpose of electronic data processing, the data will then be transferred into a database (Research Electronic Data Capture, REDCap, Vanderbilt University 2016).

If a patient does not return for a scheduled visit, every effort will be made to contact the patient. In any circumstance, every effort will be made to document patient outcome, if possible. If a patient decides to withdraw from the study, he/she will be contacted in order to obtain information about the reason for discontinuation if the patient agrees. The date and reason for the withdrawal will be recorded in the case report form (CRF). The study is registered at www.clinicaltrials.gov (NCT03831087).

### Data management {19}, methods for additional analyses {20b}, confidentiality {27}, interim analyses {21b}, auditing trial conduct {23}

Principal investigator and co-investigators will monitor observational and medical record data throughout the duration of the study and will operate independently from the funder. The principal investigator will be responsible for all aspects of the trial. All data files will be stored in a locked file cabinet inside our institution. Only the staff listed in the application will have access to the files and at no time will data files be shared with collaborators outside the institution. Patient medical record numbers will be assigned a study ID number in a master key, and study IDs will be used on all research documents. Only the principal investigator, co-investigators, and data manager will have access to the master key. We assure that any publications and presentations of the data will not allow for the identification of patients, hospitals, or physicians. Currently, there are no audits, additional or interim analyses planned.

### Composition of the coordinating center and trial steering committee {5d}, composition of the data monitoring committee, its role, and reporting structure {21a}

The current study will be coordinated by the principal investigator and the steering committee at the Medical University Innsbruck. The principal investigator will be responsible for the process of the study, the completeness of the datasets, consent forms, and correct randomization and report of adverse events.

### Protocol amendments {25}

All relevant changes and modifications to the protocol will be communicated to the contributing investigators, ethics committees, registries, and, if affected, to the trial participants.

### Ancillary and post-trial care {30}

A patient insurance covers cost for compensation of harm. After the study period, patients will receive standard of care in the outpatient setting.

### Dissemination policy {31a}, availability of data and materials {29}

If required, all participants will be informed about their respective findings by mail and can make an inquiry about their results at any time.

In the further course, it is planned to publish our results at national and international conferences as well as in a cardiovascular or radiologic journal. All co-authors of the respective work must meet eligibility criteria, i.e., each one must have significantly contributed to its content. It is planned to grant access to the full protocol on reasonable request.

### Consent for publication {32}

All study participants give written informed consent concerning study participation and publication of the respective data.

### Plans for collection, laboratory evaluation, and storage of biological specimens for genetic or molecular analysis in this trial/future use {33}

Not applicable, as there are no biological specimens collected as part of the study.

## Statistical methods {20a}

Statistical analysis will be performed with SPSS 26.0. (IBM, Armonk, NY, USA) for Windows.

Statistical analysis will be supervised by an independent statistician from the Department of Medical Statistics, Informatics and Health Economics (Innsbruck Medical University). Normally distributed continuous variables will be presented as mean ± standard deviation, not normally distributed continuous variables as median with corresponding interquartile range (IQR). Categorical variables will be displayed as the number and percentage of patients. Pearson or Spearman correlations will be calculated as appropriate. *χ*^2^-test will be used to compare categorical variables between groups. ANOVA with Bonferroni post hoc testing (if ND) and Mann–Whitney-*U* (if not ND) will be used to determine differences in continuous variables between groups. Time-to-event is defined as time from the TAVR procedure to the date of the first end-point. Kaplan–Meier survival curves will be determined and log-rank comparison will be used between groups. Uni- and multivariate Cox-regression analysis will be used to estimate hazard ratios for all left ventricular variables. Factors with univariate association with the primary end-points with significance < 0.1 will be entered in multivariate analysis. For all data a 2-tailed *p*-value of *p* < 0.05 will be considered to indicate statistical significance. No interim analysis is planned.

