### Objectives {7}

The primary objective of the present study is (a) to prove the non-inferiority of TAVR-CMR compared to TAVR-CT to plan TAVR according to clinical efficacy, defined as implantation success based on the VARC-2 criteria [37]. Secondary objectives are to prove the non-inferiority of TAVR-CMR compared to TAVR-CT to plan TAVR with regard to (b) a combined safety endpoint, based on the VARC-2 criteria [37]. Furthermore, (c) an extended clinical efficacy and safety follow-up for the non-inferiority of TAVR-CMR versus CT after 2 years as well as (d) assess imaging procedure related variables and (e) to study the accuracy of TAVR-CMR and TAVR-CT for the evaluation of patients undergoing TAVR compared to TAVR-TEE measurements.

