#### Primary endpoint

The primary outcome will be a composite clinical efficacy end-point related to implantation success at hospital discharge, based on the VARC-2 criteria [37]Absence of procedural mortalityCorrect positioning of the prosthetic valveIntended performance of the prosthetic valve (mean aortic valve gradient < 20 mmHg and no valve regurgitation > mild)

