### Sample size {14} and recruitment {15}

Sample size estimation for the primary endpoint is based on previous data indicating a rate of 4% of early deaths, 4% of valve regurgitation > mild, and 0.4% of reinterventions after TAVR [10]. Therefore, we estimate an implantation success rate of 92% in both study groups. For a non-inferiority margin of 9%, hence 113 patients per group should be included to achieve a statistical power of 80%. A drop-out rate of 10% is assumed. Therefore, it is planned to include a total of 250 patients in the trial.

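### The only stated test for categorical data is a two-sided chi-square test of difference, with no exception for the binary non-inferiority endpoint, so the stated analysis does not use the 9% margin

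*Protocol article*

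**What the plan says.** All references are to the protocol article.

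- **Objectives {7}.** The primary objective is "to prove the non-inferiority of TAVR-CMR compared to TAVR-CT to plan TAVR according to clinical efficacy, defined as implantation success" under VARC-2.
- **Primary endpoint.** "The primary outcome will be a composite clinical efficacy end-point related to implantation success at hospital discharge". Its components (no procedural death, correct position, intended valve performance) make it a success/failure outcome for each patient.
- **Sample size {14} and recruitment {15}.** The authors write that "we estimate an implantation success rate of 92% in both study groups". They continue: "For a non-inferiority margin of 9%, hence 113 patients per group should be included to achieve a statistical power of 80" per cent. No alpha and no sidedness are given there.
- **Statistical methods {20a}.** For categorical data, the chi-square "test will be used to compare categorical variables between groups". On the error level: "For all data a 2-tailed *p*-value of *p* < 0.05 will be considered to indicate statistical significance".

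The other methods listed in {20a} are correlations, ANOVA or Mann-Whitney, Kaplan-Meier with log-rank, and Cox regression. The section mentions no margin, risk difference, confidence interval or one-sided test.

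**The concern.** A non-inferiority claim needs the null hypothesis that CMR is worse than CT by at least the margin to be rejected. The chi-square test has a different null, equality of the two proportions. A large p-value from it shows only that a difference was not detected. A small one shows that the arms differ, without saying whether the deficit reaches 9 points. Neither result answers the primary objective.

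The chi-square test is the only between-group method in the section that fits a binary discharge endpoint, and the rule for categorical variables is unqualified. A reader who applies the section as written would analyse implantation success with a test that takes no account of the margin used to size the trial. The main risk is that a non-significant p-value is then reported as support for non-inferiority.

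**Working it through.** **Inputs.** Success 92% in both arms, margin 9%, 113 per group, power 80% (sample-size section); 2-tailed 0.05 (statistical methods). Assumption: the 9% is in absolute percentage points. The exact match in step 1 supports this.

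**1. Reproducing the plan's figure.** Unpooled formula for a margin-based test with true difference zero:

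n per group = (z₁₋α + z₁₋β)² × 2p(1−p) / δ², with 2 × 0.92 × 0.08 = 0.1472 and δ² = 0.0081.

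- One-sided 5%: (1.645 + 0.842)² × 0.1472 / 0.0081 = 112.4, so **113**. This matches.
- One-sided 2.5%: (1.960 + 0.842)² × 0.1472 / 0.0081 = 142.6, so **143**. This does not match.
- A test of difference sized for 92% vs 83% would need 166 (one-sided 5%) or 211 (two-sided 5%). Neither matches.

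The sample size therefore comes from a margin-based test at one-sided 5%. The methods section contains no such test, and its error level is a different one.

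**2. What the chi-square test does at 113 per arm.** Exact binomial enumeration, uncorrected Pearson test, critical value 3.84:

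| True success, CT vs CMR | P(non-significant) |
|---|---|
| 92% vs 92% | 94.7% |
| 92% vs 85% | 61.0% |
| 92% vs 83% (deficit equals margin) | 44.9% |

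**3. What a margin-based rule does on the same enumeration.** Non-inferiority is declared if the lower limit exceeds −9 points:

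| Rule | False claim at 92% vs 83% | Power at 92% vs 92% |
|---|---|---|
| Wald, 90% CI | 5.5% | 79.8% |
| Wald, 95% CI | 2.8% | 70.8% |
| Score (Farrington-Manning), one-sided 5% | 5.0% | 77.1% |
| Score (Farrington-Manning), one-sided 2.5% | 2.4% | 65.4% |

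The normal approximation agrees for Wald: SE = √(0.1472/113) = 0.0361 and 0.09/0.0361 = 2.494. Power is Φ(2.494 − 1.645) = 80.2% at one-sided 5% and Φ(2.494 − 1.960) = 70.3% at one-sided 2.5%.

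**4. How often the two approaches part company when the arms are truly equal.** With 92% in both arms, the chi-square result is non-significant while the Wald limit fails the margin in 17.5% of all trials (90% CI) or 26.6% (95% CI).

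**5. Worked example.** CT 104/113 (92.0%), CMR 98/113 (86.7%). The difference is −5.3 points. Chi-square = 1.68, p = 0.20. The Wald SE is 0.0408, so the 95% CI is −13.3 to +2.7 and the 90% lower limit is −12.0. The chi-square result is non-significant, yet non-inferiority is not shown at either level.

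**The case against.** The strongest reply is that the section never places the chi-square test beside implantation success. It reads as a generic list. Its only mention of primary end-points concerns choosing covariates for a Cox model, and that model is planned for left ventricular variables that are not among the listed endpoints. The article condenses a fuller protocol, an independent statistician supervises the analysis, and the interval method and decision rule are often left to an analysis plan. The exact match at 113 also suggests that a margin comparison was intended.

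Much of this stands. The chi-square test reaches the primary endpoint by inference, through an unqualified rule, and the absence of an interval method alone would be no finding. What remains is a positive statement: one test for categorical variables and one two-sided level for all data, neither with an exception. Both conflict with the objective and with the sample-size calculation. If an unseen plan holds a margin-based analysis, this section still contradicts it and needs correcting.

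Three stronger readings are tempting and not supported:

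- **That the investigators plan to treat p > 0.05 as non-inferiority.** No section says so, so the 45% is conditional on that misreading.
- **That the trial cannot show non-inferiority.** The data and the margin would permit it; only the stated analysis does not.
- **That p < 0.05 could wrongly condemn CMR while its interval lies inside the margin.** At 113 per arm and 92% in both arms this has a probability of about 0.000014 (90% Wald CI), or 1 in 70,000, and is negligible.

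**Conclusion.** The point holds in this form: the stated analysis of categorical data is a two-sided test of difference, it carries no exception for the non-inferiority endpoint, and as written it neither uses the margin nor can establish the primary objective. This is a conflict within the document rather than an omission.

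Its size, if non-significance were taken as non-inferiority, is a false-claim rate of about 45% at a true deficit equal to the margin, against roughly 5% or 2.5% for a margin-based rule. This rests on 113 analysed per arm, 92% success with CT, an absolute margin and an uncorrected chi-square test.

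A linked conflict has to be settled at the same time. The sample size implies one-sided 5%, whereas the methods section sets 2-tailed 0.05. The 80% power holds only for the former with a Wald-type calculation. Because this decides how the primary objective is judged, it should be corrected before the primary analysis.

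**What to change.** In the statistical methods section:

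1. Define the primary analysis as the difference in implantation success (CMR minus CT) with a score-type confidence interval, such as Miettinen-Nurminen, Farrington-Manning or Newcombe.
2. Conclude non-inferiority only if the lower limit lies above −9 percentage points.
3. State the confidence level, exempt this analysis from the general 2-tailed rule if a 90% interval is chosen, and give the same alpha and sidedness in the sample-size section.
4. Keep the chi-square test for descriptive comparisons.
5. Restate power for the level and method chosen. At 113 per group it is about 80% (Wald) or 77% (score) with a 90% interval, and about 71% (Wald) or 65% (score) with a 95% interval.

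The cost is a paragraph of text and no extra data. The downside is that the stated power may look less favourable. If the sponsor wished to keep 80% power, the formula-based requirement per group would be 126 (score, one-sided 5%), 143 (Wald, one-sided 2.5%) or 161 (score, one-sided 2.5%). That is a separate decision which the correction does not force.

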#### Secondary endpoints

Secondary end-points consist of clinical efficacy and safety end-points at discharge and 2 years.

*Combined safety end-point:*
All-cause mortalityAll strokesLife-threatening bleedingAcute kidney injury—stage 2 or 3 (including renal replacement therapy)Coronary artery obstruction requiring interventionMajor vascular complicationsValve-related dysfunction requiring repeat procedure

*Combined clinical efficacy end-point:*
All-cause mortalityAll strokeHospitalization for aortic valve related symptoms or heart failureNYHA class III or IVProsthetic valve related dysfunction (mean gradient > 20 mmHg or regurgitation > mild)

Furthermore, the two imaging strategies will be compared regarding imaging procedure related variables:Percentage of interpretable scans and scoring of image qualityPercentage of patients with need for an alternative imaging methodDuration of imaging and patient comfortCumulative radiation dose during TAVR planningCumulative amount of contrast agent used for TAVR planningImaging related safety parameters as contrast extravasation, allergic reactions, et cetera.

Finally, biomarker levels at baseline as well as at follow-up visits will be investigated.

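### The stated between-group tests for continuous variables have no baseline term, so biomarkers measured at baseline and follow-up could be compared more precisely by ANCOVA

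*Protocol article*

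**What the plan says.** In the protocol article, the section Secondary endpoints closes with the statement that "biomarker levels at baseline as well as at follow-up visits will be investigated". It names no marker, no time point and no contrast between the arms.

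The section Statistical methods {20a} gives one general rule for all continuous variables. ANOVA with Bonferroni post hoc tests (for normal data) and Mann-Whitney U (for non-normal data) "will be used to determine differences in continuous variables between groups". No baseline covariate, ANCOVA or mixed model appears. The only regression named is a Cox model. The section does not mention biomarkers, and it does not say whether a follow-up value or a change from baseline is the variable tested. A two-sided p-value below 0.05 "will be considered to indicate statistical significance".

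On allocation, the article states: "The allocation sequence is based on computer-generated random numbers without stratification".

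**The concern.** A biomarker level at follow-up usually depends in part on the same patient's level at baseline. When both are measured, that part of the between-patient spread can be removed from the comparison of the arms at no cost. The stated tests do not do this when they are applied to follow-up values: a one-way ANOVA on two arms has no covariate, and Mann-Whitney U cannot take one. With skewed data, Mann-Whitney U as described also yields a p-value without an effect estimate on the biomarker scale.

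What is at stake is precision: wider intervals and lower power for the biomarker comparisons than the collected data could give. The Bonferroni post hoc step has no role with two arms, which suggests that the sentence is a general one not fitted to a measure taken before and after the intervention.

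**Working it through.** **The plan's own figure.** The only sample size in the article concerns the binary primary endpoint: "we estimate an implantation success rate of 92% in both study groups", and "For a non-inferiority margin of 9%, hence 113 patients per group should be included to achieve a statistical power of 80"%. With n = (z₁₋α + z₀.₈)² × 2p(1−p) / margin² at one-sided α = 0.05:

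n = (1.645 + 0.842)² × 2 × 0.92 × 0.08 / 0.09² = 6.18 × 0.1472 / 0.0081 ≈ 112.4, rounded up to 113 per arm.

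This reproduces the stated number. It says nothing about biomarkers, for which no figure is given, and the present point does not alter it.

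**Inputs for the biomarker check.**
- 113 patients per arm, from the 226 to be analysed (Trial design {8}) under 1:1 allocation. Applying this number to biomarkers at follow-up is an assumption.
- Two-sided α = 0.05 (Statistical methods {20a}).
- Baseline-to-follow-up correlation ρ: not in the documents. Assumed range 0.3 to 0.8.
- Equal standard deviation (SD) at baseline and follow-up: assumed, and needed only for the change-score column.

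**Formulas.** The variance of the treatment contrast, relative to an unadjusted comparison of follow-up values (= 1), is:
- change from baseline: 2(1 − ρ)
- ANCOVA with baseline as covariate: 1 − ρ²

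The difference between the two is 2(1 − ρ) − (1 − ρ²) = (1 − ρ)², which is never negative. In large samples ANCOVA is therefore at least as precise as either alternative.

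The difference detectable with 80% power on unadjusted follow-up values is (1.960 + 0.842) × √(2/113) = 2.802 × 0.133 = 0.373 SD. For the other analyses, multiply by the square root of the relative variance.

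| Assumed ρ | Relative variance, change score | Relative variance, ANCOVA | Detectable difference, unadjusted (SD) | Detectable difference, ANCOVA (SD) | Power at an assumed 0.30 SD, unadjusted | Power at an assumed 0.30 SD, ANCOVA |
|---|---|---|---|---|---|---|
| 0.3 | 1.40 | 0.91 | 0.373 | 0.356 | 61.6% | 65.7% |
| 0.5 | 1.00 | 0.75 | 0.373 | 0.323 | 61.6% | 74.0% |
| 0.7 | 0.60 | 0.51 | 0.373 | 0.266 | 61.6% | 88.4% |
| 0.8 | 0.40 | 0.36 | 0.373 | 0.224 | 61.6% | 96.4% |

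The standard error under ANCOVA is √0.91 = 0.95, √0.75 = 0.87, √0.51 = 0.71 and √0.36 = 0.60 of the unadjusted one. These ratios are for comparisons of means. For a skewed marker they apply on the log scale, with ρ the correlation of the log values. They do not describe Mann-Whitney U exactly.

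**The case against.** The strongest objection is that the article never says biomarkers will be compared between arms by these tests. A reader might infer that the plan throws the baseline value away. The text does not support that: the rule covers all continuous variables, and ANOVA or Mann-Whitney U on change from baseline would fit it and would use the baseline. On that reading the gain from ANCOVA is small at high correlation (0.36 against 0.40 at ρ = 0.8), though larger at low correlation (0.91 against 1.40 at ρ = 0.3). This part of the objection stands, and it makes the point conditional.

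A reader might also infer that unstratified allocation lets a chance baseline difference bias the result. It does not. Randomisation keeps the unadjusted comparison unbiased, and its standard error already allows for chance imbalance. With 113 per arm the standard error of a baseline mean difference is √(2/113) ≈ 0.13 SD. In a single trial, an imbalance of that size would move an unadjusted follow-up difference by about ρ × 0.133, for example 0.7 × 0.133 ≈ 0.09 SD. ANCOVA removes this component, and that removal is the precision gain shown above. It does not correct an invalid test.

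A third inference would be that the trial's ability to see a renal effect hangs on this comparison. No biomarker is named, so renal markers can only be supposed. Acute kidney injury of stage 2 or 3 is already a component of the combined safety endpoint.

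Finally, an analysis plan that is not shown may fix the model, and the missing detail is no fault of the article. What remains is that the method the article does name is less efficient than one available from the same data.

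**Conclusion.** The point holds as an optional improvement. The one stated method for comparing continuous variables between groups has no baseline term, although biomarkers are measured at baseline. If follow-up values are compared this way, the analysis is valid but forgoes between 9% (ρ = 0.3) and 64% (ρ = 0.8) of avoidable variance. If change scores are compared, the further reduction from ANCOVA runs from 35% (1.40 to 0.91) at ρ = 0.3 to 10% (0.40 to 0.36) at ρ = 0.8.

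These sizes rest on an assumed correlation, which may well be at the lower end for visits as late as 2 years after valve replacement. They also rest on 113 patients per arm having both values. The outcome is the last listed of the secondary endpoints and is not further defined. Neither the primary endpoint nor the sample size changes.

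**What to change.** Add one sentence to Statistical methods {20a}: for biomarkers with a baseline value, the arms are compared at each follow-up visit by ANCOVA with the baseline value as covariate, on the log scale for markers that are skewed. The result is reported as the adjusted mean difference, or the adjusted geometric mean ratio for logged markers, with a 95% confidence interval. Mann-Whitney U is kept as a sensitivity analysis. It would help to list in advance which markers are to be logged, so that the effect measure does not depend on a normality check in the trial data.

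The cost is that sentence. The baseline values are already to be collected, and no extra patients, visits or measurements are needed.

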The standard procedure for the evaluation of patients for TAVR is the combination of transthoracic and transesophageal echocardiography (TTE and TEE), coronary angiography, and cardiovascular computed tomography (TAVR-CT) for the exact determination of the aortic valve dimensions, valve size, and implantation route [12]. This approach is based on the use of ionated contrast agents in three different occasions (angiography, CT, and implantation). However, up to 80% of the patients undergoing TAVR suffer from chronic renal insufficiency [13]. Reduced renal function and the amount of contrast agent used for CT have been linked to contrast induced acute kidney injury [14]. Acute kidney injury occurs in 12% of TAVR procedures and is an independent predictor of in-hospital mortality (odds ratio (OR): 4.14, CI 1.42–12.13) [15]. In Austria, 1426 (~ 17/100,000/year) TAVR procedures were performed in 2019 [16] and 24,386 (~ 29/100,000/year) TAVRs were performed in Germany in 2019, respectively [17]. Based on this data more than 17,000 patients with impaired renal function undergo TAVR each year in Austria and Germany. It can be estimated that nigh on 3000 of these patients will suffer from periprocedural acute kidney injury. As recent data have shown that 3% need in-hospital renal replacement therapy and 2% need chronic renal replacement therapy 6 months after TAVR, this sums up to 750 and 500 patients per year [18, 19]. Therefore, alternatives to reduce the need for iodinated contrast agents are desirable [20, 21]. Cardiac magnetic resonance (CMR) imaging recently has emerged as such an alternative [22, 23].

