### Trial design {8}

The present trial is a prospective, randomized, open-label trial to prove the non-inferiority of TAVR-CMR compared to TAVR-CT to guide TAVR. The final analysis will include 226 consecutive patients scheduled for TAVR. According to previous studies, approximately 45% of the patients are female [9]. Therefore, to guarantee gender equity, we aim to enroll at least 80 female patients. Patients will be randomized in a 1:1 fashion to receive a predefined TAVR-CMR protocol or to receive a standard contrast-enhanced TAVR-CT protocol within 2 weeks after inclusion. Inclusion and exclusion criteria are presented below. A detailed study flowchart is presented by Fig. 1. Follow-up for the primary objective will be performed before discharge after TAVR. Extended analysis and clinical follow-up is planned after 2 years.

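### The Kaplan–Meier and log-rank comparison of the secondary composites starts at TAVR, not at randomisation, so it omits pre-TAVR end-points and patients who never reach TAVR

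*Protocol article*

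**What the plan says.** Statistical methods {20a} of the protocol article sets the time origin in one sentence: "Time-to-event is defined as time from the TAVR procedure to the date of the first end-point". The next sentence applies it to the arms: "Kaplan–Meier survival curves will be determined and log-rank comparison will be used between groups".

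The section on sequence generation and concealment puts allocation much earlier: "Patients will undergo randomization after informed consent is given". Trial design {8} gives the timing of the allocated scan; patients are assigned to the CMR protocol or "to receive a standard contrast-enhanced TAVR-CT protocol within 2 weeks after inclusion".

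The section on secondary endpoints lists two composites, assessed at discharge and at 2 years. Both contain death from any cause and stroke; the safety composite also contains stage 2 or 3 acute kidney injury. Background and rationale {6a} explains why kidney injury belongs there: "Reduced renal function and the amount of contrast agent used for CT have been linked to contrast induced acute kidney injury".

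No section gives another time origin or says how a randomised patient without a TAVR procedure enters the time-to-event analysis.

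**The concern.** What is randomised is the planning scan. It is delivered after randomisation and before TAVR, so a clock that starts at TAVR starts after the randomised intervention has already acted. Two things follow for the log-rank comparison: end-points in the gap cannot be counted, and membership of the risk set depends on reaching TAVR, an event that comes after randomisation.

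The objectives include non-inferiority of CMR on the safety composite and on extended efficacy and safety at 2 years. A non-inferiority claim is weakened if patients who did badly before the procedure are absent from the comparison. The groups compared at TAVR no longer have the balance that randomisation provides.

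**Working it through.** **1. Order of events.** From the sections cited above: consent, then randomisation, then CMR or CT within two weeks of inclusion, then TAVR (time zero), then discharge and 2-year follow-up. The interval from randomisation to TAVR lies wholly before time zero. Its length is not stated.

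**2. What the stated rule does to each patient.**
- Event-free up to TAVR: enters at TAVR; only the waiting time is lost.
- Stroke or stage 2–3 kidney injury before TAVR, then TAVR: the first end-point precedes time zero. It is either not counted or has a negative time.
- Dies before TAVR, or never has TAVR for another reason: no time zero, so absent from the curves and the test.

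**3. Can allocation affect who reaches TAVR, and when?** The document allows for it. Under CMR and CT data analysis, valve size and suitability of the femoroiliac route are judged from each modality separately. The section on adherence foresees cross-over, and an additional CT without contrast where the CMR falls short. The secondary endpoints count patients who need another imaging method. Each can alter the timing of TAVR or whether it is done.

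**4. The plan's own figure.** There is none for the time-to-event analysis. The stated sample size concerns the binary primary endpoint: "we estimate an implantation success rate of 92% in both study groups", with a 9-point margin, 80% power and 113 per group. It reproduces at a one-sided 5% level:

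n = (z₀.₉₅ + z₀.₈₀)² × 2 × 0.92 × 0.08 / 0.09² = (1.6449 + 0.8416)² × 0.1472 / 0.0081 = 6.183 × 18.173 = 112.4, rounded up to 113.

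This number does not depend on the clock and does not change if the clock is moved.

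**5. Illustration under assumed rates.** None of these rates is in the document. Let b be the risk after TAVR, the same in both arms, and p the risk of a first end-point before TAVR. Counted from TAVR, both arms show b and the difference is 0. Counted from randomisation, the risk is p + (1 − p) × b, so the difference CT − CMR is (p_CT − p_CMR) × (1 − b).

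| b | p_CT | p_CMR | CT from randomisation | CMR from randomisation | CT − CMR (points) |
|---|---|---|---|---|---|
| 20% | 5% | 2% | 24.0% | 21.6% | 2.4 |
| 30% | 5% | 2% | 33.5% | 31.4% | 2.1 |
| 40% | 5% | 2% | 43.0% | 41.2% | 1.8 |
| 20% | 10% | 2% | 28.0% | 21.6% | 6.4 |
| 30% | 10% | 2% | 37.0% | 31.4% | 5.6 |
| 40% | 10% | 2% | 46.0% | 41.2% | 4.8 |
| 30% | 2% | 5% | 31.4% | 33.5% | −2.1 |
| 30% | 2% | 2% | 31.4% | 31.4% | 0.0 |

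As a worked line: 0.05 + 0.95 × 0.30 = 0.335; 0.02 + 0.98 × 0.30 = 0.314; difference 0.021.

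**6. Patients without a time zero, again assumed.** If 2%, 5% or 10% of the 250 randomised never reach TAVR, that is 5, 12.5 or 25 patients. The plan assumes 10% drop-out but does not say at what stage it occurs.

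**The case against.** The strongest reply is that the rule reaches less far than it first appears, and much of that stands.

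- The primary endpoint is a status at hospital discharge, sized as a proportion. The composites are also assessed at fixed visits, and a chi-square test is provided for categorical variables. The log-rank test need not be their only comparison.
- Cox regression is mentioned alongside the log-rank test, so a reader might infer that a CMR-versus-CT hazard ratio is affected. The text gives Cox regression for left ventricular variables, not for the arm contrast.
- A reader might infer that scan complications vanish. They do not: extravasation, allergic reactions and similar events are compared as imaging variables. Kidney injury is not named in that list.
- A reader might infer that the kidney injury motivating the trial is discarded. The rationale and discussion speak mainly of injury around and after the procedure and of cumulative contrast load; events from TAVR onward are still counted. Only those between randomisation and TAVR are lost.
- Eligibility requires a heart-team decision for TAVR and excludes patients with contraindications to it, which argues for few patients without TAVR.
- A clock from TAVR is natural for device performance, and visits are scheduled from TAVR.

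None of this repairs the log-rank comparison itself. The time origin is a stated rule, not a detail left to a fuller document, and no other section supplies a different one.

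**Conclusion.** The point holds for the between-arm Kaplan–Meier and log-rank analyses, read here as those of the two secondary composites because the text does not name their end-points. As defined, they compare patients selected by reaching TAVR rather than the randomised groups. This should be corrected, but it is a weakness of secondary analyses and does not bear on the primary endpoint.

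Neither direction nor size follows from the document. It is tempting to conclude that the rule works against CMR, because kidney injury after the planning CT goes uncounted. The opposite is equally open: delay or failure to reach TAVR after CMR would also go unseen, and that would hide a harm. The table above shows only that the result can move by a few points either way under assumed rates. Nor should an assumed number of pre-TAVR losses be set against the expected number of primary failures, since the primary endpoint does not use this clock.

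The conclusion rests on two things: the order randomisation, scan, TAVR, which is clear, and the possibility that the scan affects access to TAVR, which the document itself allows for. If there were no pre-TAVR end-points and every patient reached TAVR without difference in delay, the rule would do no harm.

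**What to change.** For the between-arm Kaplan–Meier and log-rank analyses, define time-to-event from the date of randomisation, for all randomised patients in their allocated arm. Count end-points that occur before TAVR. Keep patients without TAVR at risk until their event or last contact. Retain time from TAVR as a labelled supplementary analysis.

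Two drafting points go with this. First, state for each composite component from when it counts. Patients are symptomatic at entry, so NYHA class III or IV before TAVR would otherwise register as an immediate event; that component and prosthetic valve dysfunction belong to the follow-up visits. Second, Outcomes {12} schedules the 2-year visit from TAVR, so patients without TAVR need a follow-up date anchored at randomisation.

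The cost is small. Randomisation runs through REDCap, so its date should already be recorded, and the sample size is unchanged. The price is that some waiting-time events unrelated to imaging enter the composites, and that patients without TAVR must be followed up on their own schedule. A change to the reference creatinine for kidney injury is not part of this fix: the text shown gives no basis for it.
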